### Data analysis

For the assessment of feasibility, which is the primary outcome of this study, descriptive statistics will be used to assess the feasibility outcomes, such as the recruitment and retention rate of participants across the intervention. Intervention acceptability will be assessed through analysis of the level of satisfaction, opinions, and free responses related to the program described and listed.

This program is designed such that attending a total of four sessions enables participants to sequentially review their family situation including the relationships within their families and their social resources, their own, and their family members’ lives and to visualize their family relationships, burden, and the use of services. Specifically, after attending the program, participants are expected to have an improved sense of family empowerment immediately, including establishing and practicing specific and feasible plans. Therefore, to verify the effectiveness of the program, the primary outcome measure is the total FES score at T2. The secondary outcomes are to verify improvement in the levels of family empowerment (FES subscale score at T2), whether aspects directly addressed in the program had improved (caregiver burden, self-reported capability to use social resources, self-compassion at T2), and whether they had a comprehensive effect (health-related QOL at T2). Furthermore, whether any interventional effect observed at T2 is sustained (each outcome score at T3 for the early group), and whether any interventional effect observed in the early group is reproduced (each outcome score at T3 for the delayed group) is verified. The statistical analysis plan is described as follows:

The responses, wherein the outcome scores can be calculated as valid responses, are used. ITT analysis is performed to manage data from participants who deviate from the study protocol by not attending the program at the designated times as the original allocation group. First, descriptive statistics are calculated for the background attributes and outcome scores of the participants (both the participant and the child) at T1. The interval scale is used to calculate the mean and standard deviation; ordinal and nominal scales are used to calculate the frequency and proportion, and intergroup comparison is performed using Welch’s *t* test, the Mann-Whitney *U* test, and Fisher’s exact probability test.

There is a possibility of participants dropping out between T1 and T2 and between T2 and T3. Therefore, we compare the background attributes and outcome scores at T1 between the primary outcomes “total FES score of valid respondents at T2” and “non-respondents at T2 (but are valid respondents at T1)” to examine and discuss the effect caused by participants dropping out. In addition, an intergroup comparison of background attributes and outcome scores at T1 is conducted for a population of only the “total FES score of valid respondents at T2.” If group differences that may create significant bias or biased dropouts are observed in the analysis to date, we aim to consider adding those variables as covariates in subsequent analyses.

The primary analysis is an intergroup comparison using analysis of covariance with the total FES score at T1 as the covariate, and the total FES score at T2 as the dependent variable. In case of a significant interaction between the independent variable (group: early group or delayed group) and the covariate (total FES score at T1), an intergroup comparison is conducted using ANOVA without considering the scores at T1. The level of statistical significance is set as 5%. Interim analysis is not performed. Subgroup analysis is conducted for children with severe disabilities, children with disabilities who need constant medical care, and single-parent households. We also examine whether the increase in the total FES score from T1 to T2 is clinically significant. However, the clinical minimum significant difference for FES is not clear; therefore, this is discussed through a comparison with a previous study [12].

An intergroup comparison is similarly conducted for the secondary outcomes using the analysis of covariance for each outcome at T2. The results at T1 and T3 for the early group are examined using a paired *t* test to determine whether the intervention effect observed at T2 is sustained. The results at T2 and T3 for the delayed group are examined using a paired *t* test to determine whether the intervention effect observed in the early group is reproduced in the delayed group.

The following two analyses are conducted as a sensitivity analysis of the primary analysis. The first is a re-analysis of the dropouts from T1 to T2 with the amount of change in the total FES score set as 0, to consider the effect of dropouts. The second is a per-protocol analysis. That is, re-analysis is conducted to compare the results of participants who attended all four sessions of the program (group) to all others (group).

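### Dropout between T2 and T3 is named as a concern, but every dropout check stops at T2, so the secondary T3 conclusions rest on paired t tests in whoever still answers

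*Protocol article*

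**What the plan says.** The Data analysis section of the protocol article acknowledges loss in both intervals: "There is a possibility of participants dropping out between T1 and T2 and between T2 and T3". The steps it draws from this are all tied to T2:

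- The attrition check compares T1 characteristics of those with a valid total FES score at T2 with those of "non-respondents at T2 (but are valid respondents at T1)” to examine and discuss the effect caused by participants dropping out".
- The between-group balance check "is conducted for a population of only the “total FES score of valid respondents at T2".
- If either check shows a problem, "we aim to consider adding those variables as covariates in subsequent analyses".
- The dropout sensitivity analysis is attached to the primary comparison only: "The first is a re-analysis of the dropouts from T1 to T2 with the amount of change in the total FES score set as 0".

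Two further questions are put to the T3 data. In the early group, T1 and T3 are compared by a paired t test "to determine whether the intervention effect observed at T2 is sustained". In the delayed group, T2 and T3 are compared by a paired t test to see whether the effect is reproduced. Valid responses are used throughout. Under Feasibility outcomes, retention through T3 is a stated outcome, to be summarised descriptively.

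**The concern.** The plan identifies two intervals of loss and deals with one. A paired t test of T1 against T3, or of T2 against T3, uses only families with both scores. The effect at T2 and its persistence are therefore judged in different sets of families, and nothing compares those lost after T2 with those who stay, although their T1 scores, and usually their T2 scores, are already in hand.

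At stake are two secondary conclusions that the plan says these tests will verify. In the early group, if T3 response depends on the gain seen at T2, the families who remain are those who gained more, and persistence looks better than it is. In the delayed group the mechanism differs. According to the Data collection method section, its T2 falls just before its program starts and its T3 just after the program ends. Loss between T2 and T3 is therefore its dropout during the program, and no planned analysis examines it.

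**Working it through.** **What is covered at each interval**

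| Step | T1 to T2 | T2 to T3 |
|---|---|---|
| Named as a risk | yes | yes |
| Respondents compared with non-respondents | yes | no |
| Group balance among respondents | yes | no |
| Dropout re-analysis | yes (change set to 0) | no |
| Descriptive retention rate | yes | yes |

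The covariate option does not fill the right-hand column. It is triggered by the T2 checks, it is only something to be considered, and a plain paired t test takes no covariates.

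**How many families are involved.** The plan gives no figure on this point to reproduce. From the Sample size section I take N = 52 and 10% dropout; an equal split, 26 per arm, is my assumption. The plan does not say over which interval the 10% applies.
- Once over the whole study: 26 × 0.90 = 23.4, so about 23 pairs per arm at T3.
- Per interval: 26 × 0.90² = 21.1, so about 21 pairs (19% missing).

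**Size of the early-group bias (illustration).** Assumed, not in the documents: score SD 1; correlation 0.7 between time points, so the SD of a change is √(2 × 0.3) = 0.77; correlation 0.6 between the T1-T2 and T1-T3 changes; true T3 gain 0.33 SD; log-odds of T3 loss falling by 0.7 to 1.5 per SD of the T2 change. The T2 gain is set to 0.66 SD (the plan's 0.33 read as Cohen's f and doubled); the bias does not depend on it.

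Bias of the completer mean = 0.6 × 0.77 × (mean standardised T2 change among those who stay). At 10% loss, simulation puts that last term at 0.067 (slope 0.7) and 0.121 (slope 1.5):
- 0.6 × 0.77 × 0.067 = 0.031 SD
- 0.6 × 0.77 × 0.121 = 0.056 SD

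| Loss by T3 | Completer gain (true 0.33) | Excess |
|---|---|---|
| 10% | 0.36-0.39 | 0.03-0.06 |
| 20% (assumed) | 0.39-0.44 | 0.06-0.11 |
| 30% (assumed) | 0.42-0.48 | 0.09-0.15 |

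Regressing the T3 change on the T2 change and averaging over all families, including those lost, returns 0.33 in every row, because loss here depends only on an observed score.

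**Against the noise.** With 23.4 families the standard error is 0.77/√23.4 = 0.16 SD, so the excess at 10% loss is roughly a fifth to a third of one standard error. If no gain truly remains at T3, the chance of a significant positive result from a two-sided 5% test is about 4-5% at 10% loss, instead of 2.5%.

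**Would the plan's own zero-change rule help at T3?** Take a completer result that is just significant (p = 0.0500) and add zeros for those lost.
- 23 of 26 observed: standardised mean 0.432 becomes 0.432 × 23/26 = 0.38; p = 0.0503.
- 21 of 26 observed: 0.455 × 21/26 = 0.37; p = 0.0506.

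The mean and its standard error shrink together. In the simulation the false-positive rate is about 3.8% with or without the zeros (10% loss, slope 0.7), and about 13% with or without them (30% loss, slope 1.5).

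**Delayed group.** The simulation does not carry over. This group's T2 precedes its program, so there is no program gain at T2 for loss to depend on. Loss would more plausibly follow the response to the program, which is unobserved in those who leave.

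**The case against.** The best defence is one of priority. This is a feasibility study, effectiveness is a secondary objective, and the effectiveness endpoint is total FES at T2. Concentrating the dropout work there is reasonable, and the sensitivity analyses are labelled as belonging to the primary analysis. Reminders are sent, and everyone is asked to answer regardless of attendance. This lowers the weight of the point but does not remove it: the plan itself names T2-T3 loss and then provides no analysis of it. Nor is this detail left to a fuller document, because the article sets out the checks, tests and re-analyses itself.

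Three stronger readings are tempting, and the documents do not support them.
- A reader might infer that persistence could be overstated by nearly half (0.15/0.33 = 46%), with false positives near 13%. Those values need 30% loss and the steepest slope, both assumed. The only stated rate is 10%, and even 10% per interval gives 19%.
- A reader might infer that the replication result is biased by a similar amount. No figure is available for the delayed group; what can be said is that its on-program dropout is not examined.
- A reader might infer that the plan is blind to T3 loss. It will report retention through T3, so the extent of loss will be visible. What stays hidden is whether those lost differ from those who stay.

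It is also true that no passage says families who gained little are less likely to answer at T3. That is a possibility to be checked.

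**Conclusion.** The point holds for the secondary T3 analyses. The plan names loss between T2 and T3 but neither compares those lost with those who stay nor tests how far the T3 conclusions depend on them. In the early group, if T3 response depends on the T2 gain, the completer-only estimate overstates persistence by about 0.03-0.06 SD at 10% loss, with false positives of about 4-5% instead of 2.5%, and by more if loss is higher. These sizes rest on the assumed correlations and loss slopes. For the delayed group the gap is established from the text alone, without a size. The T2 primary comparison is untouched, so this is minor to moderate.

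**What to change.** In the Data analysis section:

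1. Repeat the respondent versus non-respondent comparison at T3 within each arm, using T1 and T2 scores and, in the early group, the T1-T2 change in FES. This is the essential step.
2. Estimate the T3 contrasts (T1 to T3 in the early group, T2 to T3 in the delayed group) from a mixed model on the T1, T2 and T3 scores, so that families with T2 but no T3 stay in. State that it corrects only for loss that depends on observed scores.
3. Add a delta-adjusted sensitivity analysis in both arms: shift the model-based T3 values of those lost downwards by a range of amounts and report the shift at which the conclusion changes. Do not simply extend the zero-change rule to T3, since it shrinks the estimate but hardly moves the test.

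The cost is revised wording and a little more analysis on data already being collected. No new visits, questionnaires or participants are needed.

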### Sample size

The sample size is estimated by selecting *F* tests (ANCOVA) using G*Power software version 3.1.9.7 [14]. The required sample size is calculated based on data obtained from the pretest implemented with the same subjects and equivalent program content as used in this study. The required sample size is 52, assuming an effect size of 0.33, a test power of 80%, and an *α* value of 0.05. The dropout rate is assumed to be 10% based on a previous study with an online program for parents of children with disabilities [15]. From a feasibility study perspective, a formal sample size calculation is not essential. Our sample size calculation is based on the pragmatics of recruitment and the necessity for examining feasibility among a broad group of families caring for children with disabilities.

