### Intervention allocation

Participants are allocated to the early or delayed group in the order of their applications. A maximum of 20 people can participate in each program, and the family empowerment program comprising a total of four group sessions is implemented several times per month. Participants in both groups will not be told the timings of the intervention or the evaluations in the other group in an attempt to keep all participants blinded as to which group they are allocated to. Facilitators of the family empowerment program cannot be blinded to the participants’ allocations because they need to contact the participants and respond to inquiries. The analysts are blinded to the allocation of participants.

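### When the group-by-T1 interaction is significant, the primary effectiveness analysis drops T1 FES, the only covariate it commits to in a non-randomised trial; the interaction should be modelled instead

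*Protocol article*

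**What the plan says.** The protocol article, Data analysis, defines the primary analysis as "analysis of covariance with the total FES score at T1 as the covariate, and the total FES score at T2 as the dependent variable". It then sets a switch, triggered when group and T1 FES interact significantly. The replacement analysis is given in these words: "an intergroup comparison is conducted using ANOVA without considering the scores at T1". The significance level is given once, as 5%, and no separate level is set for the interaction test.

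Under Intervention allocation: "Participants are allocated to the early or delayed group in the order of their applications". Other variables that differ between groups may be considered as covariates, but only tentatively. The two sensitivity analyses concern dropout (change set to 0) and attendance at all four sessions. So no baseline-adjusted estimate of the primary comparison is specified for the case where the switch is made.

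**The concern.** A significant group-by-T1 interaction means that the group difference varies with initial FES. That makes a single common-slope estimate incomplete. It does not make T1 irrelevant. An ANOVA without T1 still averages over the varying effect, and it also gives up control of T1 differences between the groups.

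That control matters more here than in a randomised trial. Early and late applicants may differ in empowerment, and T1 FES is the only covariate to which the primary model is committed. The rule removes it on the strength of a preliminary test on the same small sample. What is at stake is the primary effectiveness estimate in those trials where the test is significant.

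**Working it through.** **Inputs from the protocol article.** ANCOVA on T2 FES with T1 FES; switch to ANOVA on a significant interaction (taken as tested at 5%); total sample 52, effect size 0.33, power 80%, α 0.05 (Sample size).

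**Assumptions, because the documents give no figure.** Equal arms (26 each); T1–T2 correlation r = 0.5 to 0.8; equal SDs at T1 and T2, so the common slope in SD units is r; T1 group difference D = 0 or ±0.3 SD (0.5 SD as a larger case).

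**Starting power.** The plan gives no figure for the fallback itself. Its sample-size figure does not reproduce: reading 0.33 as Cohen's f, the noncentral F for ANCOVA (λ = f²N, denominator df N − 3) needs N = 75 for 80% power and gives 64.5% at N = 52. That is a separate matter, and the present point does not depend on it. It explains why the ANCOVA power below starts near 62%, not 80%.

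**Shift in the estimate.** With slopes b₀ and b₁, equal arms and δ the effect at the overall mean T1, the raw T2 difference has expectation δ + D × (b₀ + b₁)/2. With equal slopes this is δ + r × D.
- D = 0.3 SD: 0.5 × 0.3 = 0.15; 0.7 × 0.3 = 0.21; 0.8 × 0.3 = 0.24 SD.
- D = 0.5 SD: 0.25, 0.35 and 0.40 SD.
- The sign follows the sign of D. At D = 0 the shift is zero.

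In simulation, the interaction model evaluated at mean T1 averages about 0.00 in all of these no-effect cases. An ANOVA at a nominal 5% rejects 8.2% to 13.4% of the time at D = 0.3 SD over this range of r.

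**Loss of precision.** Residual variance is multiplied by 1/(1 − r²): 1/0.75 = 1.33, 1/0.51 = 1.96, 1/0.36 = 2.78. At N = 52, f = 0.33 and balanced T1, ANCOVA power is 64.5%; ANOVA power is 52.4%, 38.5% and 28.8% at r = 0.5, 0.7 and 0.8.

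**How often the rule fires, and the overall effect.** With equal slopes the interaction test is significant in about 5% of trials. Overall type I error of the two-stage rule is then about 5% to 6.4%, the top of that range being at r = 0.8 and D = 0.5 SD.

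Now let the slopes differ by an assumed 0.3, with r = 0.7 and an effect of 0.47 SD (2 × 0.33 × √(1 − 0.49) = 0.66 × 0.714 = 0.47). The rule fires in about 30% of trials. Overall power:

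| T1 difference | ANCOVA throughout | Rule as written |
|---|---|---|
| 0 | about 62% | about 55% |
| −0.3 SD (early group lower) | about 61% | about 48% |
| +0.3 SD (early group higher) | about 61% | about 63% |

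The last row is no gain: the extra rejections come from upward bias.

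**A larger slope difference.** With slopes 0.7 and 0.3 the mean slope is 0.5 and the rule fires in about 47% of trials. For a true effect of 0.5 SD, the ANOVA averages 0.5 + 0.5 × 0.3 = 0.65 or 0.5 − 0.5 × 0.3 = 0.35 at D = ±0.3 SD. The interaction model at mean T1 gives 0.50 both times.

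**The case against.** The rule is pre-specified, so the analyst has no free choice. Equal slopes are a standard condition for ordinary ANCOVA, and it is reasonable to provide for their failure. T1 scores are to be compared between groups, so an imbalance would be seen. Feasibility is the study's primary outcome, effectiveness is a secondary objective, and the Sample size section calls a formal calculation inessential.

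Three stronger readings are tempting, and the documents do not support them.
- **A reader might infer that the fallback always gives a biased and weaker result.** Bias needs a T1 difference. Allocation by application order does not prevent one, but does not show one either. With balanced T1 the ANOVA is unbiased, and with an imbalance favouring the early group it can reject more often.
- **A reader might take the 8.2% to 13.4% rejection rates as the trial's error rate.** They describe the ANOVA itself. With equal slopes the rule seldom reaches it.
- **A reader might conclude that the study cannot proceed without this change.** No feasibility result depends on the rule.

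What does not stand is the remedy. Pre-specifying the switch does not make dropping T1 a cure for unequal slopes. Seeing a T1 imbalance does not put T1 back into the model, and the provision for extra covariates is tentative, while the fallback expressly leaves T1 out.

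**Conclusion.** The fallback is wrong as written and should be fixed. Its harm falls on trials in which the interaction test is significant: the estimate moves by about the mean slope times the T1 difference, in either direction, and precision is lost even when T1 is balanced. At an assumed 0.3 SD difference the shift is 0.15 to 0.24 SD, set against an effect of about 0.47 SD if 0.33 is Cohen's f and r = 0.7. Overall type I error is hardly affected when slopes are equal. Overall power changes materially only if slopes truly differ, and then it depends on the imbalance. The correlation, the T1 difference and the slope difference are all assumptions. The direction of the argument does not depend on them, but the sizes do. The point ranks below one that must be fixed, because it concerns the primary effectiveness analysis and not the feasibility outcome.

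**What to change.** Delete the ANOVA fallback and state that T1 total FES stays in the primary model in every case. If the interaction is significant, add group × (T1 minus overall mean T1) and report the adjusted group difference at mean T1 with its 95% CI. Say the same for the secondary outcomes if the fallback was meant to carry over to them. Robust standard errors and effects at the T1 quartiles are optional.

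The cost is one sentence in the analysis plan and one degree of freedom when the interaction term is used. No further data or participants are needed.

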The mental health of mothers raising children with disabilities is related to their empowerment. Previous research has shown that depressive symptoms are associated with lower empowerment among mothers raising children with disabilities [8]. Also, mothers raising children with developmental disabilities participated in health-promoting activities infrequently; moreover, depressive symptoms, maternal empowerment, and two indicators of child-related QoL explained significant variance in healthy behaviors [9]. Parents often face a variety of difficulties in raising children with disabilities. Therefore, these parents need to be able to not only receive social resources including healthcare services but also use and coordinate social resources that are necessary for their children and families. In addition, these parents need the skills to cope with child- and family-related problems.

In a previous study, we conducted in-depth interviews with 34 families with children with severe disabilities who lived at home (mother, father, and siblings aged 12 years and older) [10] and conducted a questionnaire survey of 158 nurses and government officials using the Delphi method [11] to comprehensively list the factors that comprise the family empowerment model. Thereafter, we issued a self-administered questionnaire based on that model to 1659 families nationwide with children with severe disabilities who were living at home, to develop and verify the family empowerment model [12]. This research undertaken with family caregivers has shown an association between the empowerment and knowledge of social resources and how to use these resources in order to reduce burden. However, the above were observational studies. In this study, we verify, through implementational research, whether an intervention for each of these factors (specifically, by working on increasing the “self-reported capability to use social resources” and reducing the “caregiver burden”) can actually increase family empowerment. Furthermore, we aim to determine which of the three levels of Koren et al.’s conceptual framework (“family [internal] FA”, “service system SS,” and “community SP”) are actually empowered by this intervention.

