## Method

### Study design and setting

This study is a non-randomized, waitlist-controlled trial. We compare the group starting the family empowerment program a week after the initial evaluation (intervention/early group) to the group starting delayed intervention (waitlist-controlled/delayed group). This study is registered as a clinical trial in the UMIN Clinical Trials Registry (UMIN000044172). The study protocol has been prepared in accordance with the Standard Protocol Items: Recommendations for Intervention trials (SPIRIT) 2013 statement [13]. The trial and flow of participants through the trial are illustrated in the flow chart (Fig. 1). The SPIRIT schedule of enrollment, interventions, and assessments are presented in Fig. 2. The SPIRIT Checklist can be found in Additional file 1. This protocol is version 1, dated June 2021.

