### Data collection method

In order to evaluate the effectiveness of this program, data is collected from participants through an online survey. Participants are invited to complete online questionnaires that assess their family empowerment, caregiver burden, self-reported capability to use social resources, self-compassion, and quality of life. A survey request email is sent to the participants regarding the online survey at the times described below, and one or more reminders are sent to those who do not respond. Participants are requested to cooperate in the survey regardless of their program attendance. For example, even if a participant does not attend any sessions, they are asked to complete the survey.

The online survey is conducted at the following three time points. After the participants apply for the program and are allocated to either the early or delayed group, they are notified of their attendance month (from July to December). At the time, participants are not informed if they are in the early or delayed group; they are simply notified of their attendance month to prevent response bias based on the participant’s impression of their allocated group. Thereafter, the initial evaluation (Time 1 [T1]) is conducted before the early group starts the first session. For the early group, this corresponded roughly to a week before attending the program. The post-intervention evaluation (Time 2 [T2]) is conducted immediately (within 1 week) after the early group completed all four sessions in the program (4 weeks). The follow-up evaluation (Time 3 [T3]) is conducted 4 weeks after the post-intervention evaluation. The timings are the same for the delayed group; however, it begins the program precisely 4 weeks after the early group does. That is, the delayed group completes the evaluation for T1 roughly 5 weeks before attending the program, T2 immediately before attending the program, and T3 immediately after completing the course.

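### Clinical importance is to be discussed on the T1-to-T2 rise in total FES, with no arm or comparator named, although the primary ANCOVA already gives a controlled estimate

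*Protocol article*

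**What the plan says.** Study design and setting gives the design: "This study is a non-randomized, waitlist-controlled trial". Data collection method puts both groups on the same evaluation dates, with the delayed group starting four weeks after the early group. For the delayed group this means "T2 immediately before attending the program, and T3 immediately after completing the course". Its T1-to-T2 interval, roughly five weeks, therefore contains no session.

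The Data analysis section uses that comparator for efficacy: "The primary analysis is an intergroup comparison using analysis of covariance with the total FES score at T1 as the covariate", with total FES at T2 as the dependent variable. Later in the same paragraph it turns to clinical importance: "We also examine whether the increase in the total FES score from T1 to T2 is clinically significant". It then concedes that "the clinical minimum significant difference for FES is not clear; therefore, this is discussed through a comparison with a previous study". The study cited there is the team's nationwide questionnaire survey. The Background describes that survey together with the team's other preparatory work and says of them all: "However, the above were observational studies".

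**The concern.** The primary analysis and the clinical-importance step look at different quantities. The first is a between-group contrast. The second, as worded, is a before-after change with no reference group. Nothing else in the article ties clinical importance to the between-group difference.

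A before-after change adds together what the programme did and what would have happened anyway. Here the second part could include the effect of answering the same self-report scale again within weeks, and of anticipating the programme. The waiting group is there to measure that part, and the sentence does not use it. What is at stake is how the size of the benefit is described: a reader of the results could be told that a rise is meaningful when part or all of it also occurred in families who had not yet attended.

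**Working it through.** **The plan's own figure.** The article gives no figure for this step: no minimum important difference, no FES standard deviation and no expected change on the waiting list. There is nothing to reproduce, so the check is on which quantity is used.

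**Decomposition.** Let *e* be the programme effect on total FES at T2, and *c* the T1-to-T2 change that would occur without the programme. Take *c* as common to both groups.

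- Early-group rise = *c* + *e*
- Delayed-group rise = *c*
- Early minus delayed = (*c* + *e*) − *c* = *e*

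The early-group rise therefore misstates the effect by exactly *c*, upward if *c* is positive and downward if negative. The sentence names no arm. If the two groups were pooled at equal size, the rise would be (*c* + *e* + *c*)/2 = *c* + *e*/2, which still contains *c* and also halves *e*.

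**Illustration, in SD units.** The values of *c* are assumed; the documents support none of them. For *e*, the Sample size section gives an effect size of 0.33. Read as Cohen's f with two equal groups, this is d = 2 × 0.33 = 0.66 residual SD.

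| Assumed *c* | Early rise if *e* = 0 | Early rise if *e* = 0.66 | Between-group difference |
|---|---|---|---|
| 0.1 | 0.10 | 0.76 | 0 or 0.66 |
| 0.2 | 0.20 | 0.86 | 0 or 0.66 |
| 0.3 | 0.30 | 0.96 | 0 or 0.66 |

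Relative to 0.66, the excess is 0.1/0.66 = 15%, 0.2/0.66 = 30% and 0.3/0.66 = 45%. These percentages hold only if *c* and the 0.66 are in the same SD unit.

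**Precision of the controlled estimate.** Assume the 52 participants split 26 and 26; the article states no split. With one covariate there are 52 − 2 − 1 = 49 residual degrees of freedom, and the 95% CI half-width is t(0.975, 49) × √(2/26) = 0.557 residual SD. This shows why the interval should accompany any statement about importance. It is not evidence that the plan would withhold one.

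**Dependence on the sample size.** The stated inputs (f = 0.33, 80% power, α = 0.05) give 75 rather than 52 with a noncentral-F ANCOVA calculation using two groups and one covariate. That is a separate matter. The decomposition above does not use the sample size.

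**The case against.** The strongest reply is that the sentence is being read too hard. It begins as an addition to the primary analysis, it does not say the delayed group is ignored, and the delayed group's change is measured and can be set beside the early group's. Minimum important differences are often defined on within-person change, so looking at change from baseline is not in itself a mistake. The step has no threshold and no test, and the trial's primary outcome is feasibility.

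Much of this stands, and it rules out several stronger readings that a reader might infer:

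- **That the rise replaces the ANCOVA result, or that success could be declared on it after a null primary analysis.** The article does not say so. Effectiveness is verified by the between-group comparison at T2, and the clinical-importance step is only a discussion.
- **That regression to the mean or season inflates the rise.** Entry requires no FES cut-off, and T1 to T2 spans only about five weeks. Neither mechanism is established by the documents.
- **That the benchmark is invalid.** The Background supports calling the earlier survey an observational questionnaire study, but the article does not say which quantity will be taken from it, and the survey is not available to check.
- **That the overstatement is 15% to 45%.** That range comes entirely from the assumed waiting-list change.

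What the reply does not remove is that the article does name the quantity to be judged, and that quantity has no comparator. This is a stated choice, not a detail left to a fuller document.

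**Conclusion.** The point holds in limited form. As worded, the clinical-importance discussion rests on a change that includes whatever would have happened without the programme, while a less biased estimate is already produced by the primary analysis. The distortion equals *c*, whose size and sign cannot be found in the documents.

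The consequence is confined to a secondary interpretive statement. The primary test, the feasibility outcome and the conduct of the trial are unaffected, so this is a correction of wording and not a flaw in the design.

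The conclusion assumes that the sentence means a before-after change, which is its plain reading, and that *c* is broadly common to the two groups. The second assumption is imperfect. Participants are allocated by order of application, so the adjusted difference may still be confounded. The textbook is posted about a week before a group's first session, so delayed families may hold it by T2. The adjusted difference nevertheless removes change shared by both groups, which the rise alone cannot do.

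**What to change.** Replace the sentence with wording such as: *Clinical importance will be discussed on the ANCOVA-adjusted early-minus-delayed difference in total FES at T2 with its 95% confidence interval, in FES points and in units of the T1 standard deviation observed in this trial. The T1-to-T2 change in each group will be reported side by side as description only.*

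Taking the SD from the trial's own T1 data avoids relying on the earlier survey, which the Background describes as covering families of children with severe disabilities, a narrower population than this trial enrols. The comparison with that survey can stay as context. The plan switches to an ANOVA without T1 scores if the group-by-baseline interaction is significant, so the text should also say which between-group estimate is discussed in that case. A sentence should acknowledge that allocation by order of application leaves possible confounding.

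The cost is wording only: no new data and no new model, because the primary analysis already supplies the estimate and its interval.
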